[figure not shown]

| Date                                                            | 8 th May 2020                                                                                                                                                                                                                                                                                                                                                                                               |
| Version                                                         | Protocol version 01                                                                                                                                                                                                                                                                                                                                                                                                    |
| Title                                                           | Hydroxychloroquine efficacy and safety in preventing SARS-CoV-2 infection and COVID-19 disease severity during pregnancy                                                                                                                                                                                                                                                                                               |
| Country                                                         | Spain                                                                                                                                                                                                                                                                                                                                                                                                                  |
| Study drugs                                                     | Hydroxychloroquine: 400mg/day during three days, followed by 200mg/day during 11 days
Placebo: two tablets during three days, followed by 1 tablet/day during 11 days                                                                                                                                                                                                                                               |
| Intervention duration                                           | 14 days, followed by a follow-up visit 7 days post intervention (day 21)                                                                                                                                                                                                                                                                                                                                               |
| Study drugs provided by                                         | Laboratorios Rubió                                                                                                                                                                                                                                                                                                                                                                                                     |
| Phase of clinical trial                                         | Phase IIIb                                                                                                                                                                                                                                                                                                                                                                                                             |
| Main objectives                                                 | 1. To assess the effect of HCQ in reducing SARS-CoV-2 viral shedding by PCR in infected pregnant women with mild symptoms.
2. To assess the efficacy of HCQ to prevent incident SARS-CoV-2 infection in pregnant women in contact with an infected or suspected case.
3. To evaluate the effect of HCQ in preventing the development of the COVID-19 disease in asymptomatic SARS-CoV-2-infected pregnant women. |
| Study design                                                    | Randomized double-blind placebo-controlled multicentre clinical trial                                                                                                                                                                                                                                                                                                                                                  |
| Study population and sample size                                | Pregnant women with and without mild symptoms/signs of SARS-CoV-2 infection and close contacts of confirmed or suspected cases and meeting inclusion criteria.
714 will be recruited                                                                                                                                                                                                                                |
| Disease in study                                                | SARS-CoV-2 infection and COVID-19 disease                                                                                                                                                                                                                                                                                                                                                                              |
| Ethics committee that evaluated and approved the clinical trial | Ethics Committee of the Hospital Clinic de Barcelona                                                                                                                                                                                                                                                                                                                                                                   |
| Sponsor                                                         | Barcelona Institute for Global Health (ISGlobal),
Hospital Clínic - Universitat de Barcelona
[name]
[name], Spain                                                                                                                                                                                                                                                              |

## List of abbreviations

|      |                             |
|------|-----------------------------|
| ANC  | Antenatal care              |
| ECG  | Electrocardiogram           |
| HCQ  | Hydroxychloroquine          |
| US   | Ultrasound                  |
| WHO  | World Health Organization   |
| eCRF | Electronic Case Report Form |
| PCR  | Polymerase Chain Reaction   |

## Synopsis

The emergence of severe acute respiratory syndrome coronavirus 2 (SARS-CoV-2) disease (COVID-19) in China at the end of 2019 has caused a large global outbreak and is a major world public health issue. Since the onset of the SARS-CoV-2 epidemic, very few studies have reported on the effects of the infection on maternal health. Importantly, pregnant women should be considered a population at increased risk of infection, given the greater risk of severe morbidity and mortality from SARS and influenza. Pregnancy is considered a period of susceptibility for infections, including respiratory pathogens and severe pneumonia. Regarding SARS-CoV-2 it is still unclear how the infection affects pregnant women and their offspring, as well as which factors may influence maternal disease and outcomes.

This is a randomized, double blinded, placebo-controlled multicentre clinical trial including 714 pregnant women (200 SARS-CoV-2 infected -100 symptomatic with mild disease and 100 asymptomatic- pregnant women and 514 SARS-CoV-2 uninfected pregnant women who are contacts with a SARS-CoV-2 case) with the main objectives of assessing the safety and efficacy of oral hydroxychloroquine (HCQ) in reducing maternal viral shedding by PCR, and preventing incident SARS-CoV-2 infection and disease severity. Pregnant women undergoing antenatal follow up at five maternity hospitals, presenting at least one sign and/or one mild suggestive symptoms and a positive SARS-CoV-2 PCR test, or who are contacts of a suspected or confirmed case, will be recruited and randomised 1:1 to receive HCQ orally (400 mg/day for 3 days, followed by 200 mg/day for 11 days) or placebo. Women will be followed up for the duration of the intervention. One week after intervention completion, a SARS-CoV-2 PCR test will be repeated. At delivery, the pregnancy outcome will be registered and a cord blood sample will be collected to measure for IgG and IgM of SARS-CoV-2. A neonatal nasopharyngeal aspirate will be collected to perform PCR SARS-CoV-2 testing.

## COVID-Preg flow and design

[figure not shown]

## 1. Background

The outbreak of severe acute respiratory syndrome coronavirus 2 (SARS-CoV-2) and its disease named COVID-19 that started in November 2019 in Wuhan (China) has rapidly spread worldwide (1) and was declared a pandemic of Public Health Emergency of International Concern by the World Health Organization (WHO) in March 2020.

Globally, epidemiological data is being reported as total number of laboratory-confirmed cases and associated deaths; but limited information exists regarding the prevalence and incidence of infection among pregnant women. Additionally, there is insufficient data to estimate if pregnant women are at an increased risk of getting infected from, and/or to develop severe health outcomes, compared to the general population (2).

Pregnancy is a period of susceptibility for infections, including respiratory pathogens and severe pneumonia (3,4). Thus, pneumonia from any infectious aetiology is an important cause of morbidity and mortality in pregnant women, being reported as the 2nd and 3rd most common cause of indirect maternal death in some studies (5,6). It is estimated that about 25% of pregnant women that develop pneumonia will need to be hospitalized in critical care units and require ventilatory support (7). Although bacterial pneumonia may be a serious disease when it occurs during pregnancy viral pneumonia has even higher levels of morbidity and mortality during pregnancy (8). Differential severity and mortality rates in pregnant patients have been reported in epidemics, such as the 1918 influenza pandemic (27% in pregnancy vs. 2,6% in non-pregnant adults-higher if infected in the 3rd trimester-) (9), 2009 H1N1 influenza (4 times more likely to be admitted to hospital) (10), and 2003 SARS (50% of pregnant women infected were admitted to intensive care, 33% required mechanical ventilation, and 25% mortality rate) (11). The commonest adverse obstetrical outcomes associated with maternal pneumonia from all causes include preterm labour, intrauterine growth restriction (IUGR), stillbirth and neonatal death (7).

The limited information regarding the effects of coronavirus infections during pregnancy results from the epidemics of severe acute respiratory syndrome (SARS) and the Middle East respiratory syndrome (MERS) (12). These two diseases might provide insights into the effects in pregnancy of the new epidemic of coronavirus disease 2019 (COVID-19). The experience with SARS and MERS suggests that both infections are associated with poor maternal and fetal-neonatal outcomes, including severe maternal disease requiring hospitalization, intensive care and ventilator support as well as preterm delivery, IUGR, spontaneous abortion and perinatal death; importantly, the data available indicates that the severity of the disease is worse in pregnant women than in infected non-pregnant women (3). On the other hand, intrauterine maternal-fetal transmission of these two infections has not been documented (3).

Regarding COVID-19, very limited data still exists about its effects in pregnancy. The few reports available of pregnant women infected with COVID-19, all were infected in the third trimester and clinical features were similar to those in non-pregnant adults, with fetal distress and preterm delivery seen in some cases. All women delivered by caesarean section and the newborns tested negative for SARS-CoV-2 (3).

On the other hand, according to the World Health Organisation, there is currently no medication shown to be effective for the treatment or prevention of the SARS-CoV-2 (13).

Early *in-vitro* studies after the SARS 2003 epidemic showed that chloroquine (CQ) had a strong *in-vitro* antiviral effect on SARS-CoV infection of primate cells (14) (13). More recently, an inhibitory *in-vitro* effect of CQ has been shown on the SARS-CoV-2 (15). In addition, *in-vitro* studies comparing CQ with hydroxychloroquine (HCQ) on SARS-CoV-2 infected cells showed that HCQ had a more potent inhibitory effect than CQ (14). These findings led to clinical studies in

China with encouraging results and to include CQ in the recommendations regarding prevention and treatment of the infection in this country (16). In other countries suffering the epidemic (such as Spain) HCQ is currently used to treat admitted patients with SARS-CoV-2 infection. Preliminary unpublished results of a French clinical trial in 24 infected patients showed a clearance of the virus in 75% of those treated with HCQ for 6 days compared with 10% in untreated controls (17)

Chloroquine and HCQ are used in the treatment of systemic lupus erythematosus (SLE) and rheumatoid arthritis (RA) for more than 25 years including in pregnant women (18). The safety of this treatment has been well established during pregnancy. In addition, there is wide evidence of the safety of CQ in the treatment and prevention of malaria in pregnancy in endemic areas (19). Complete rationale for drug selection and dosage are included in Annex 1.

## **2. Justification**

It still unclear how SARS-CoV-2 affects pregnant women and their offspring, as well as which factors may influence obstetrical disease and outcomes, including the timing of maternal viral exposure by gestational age, the effects of parity, age, host immune responses, coexisting medical and obstetrical conditions and the effects of treatment regimens. While further information is gathered, based on the existing evidence from other infections causing pneumonia, pregnant women should be considered to be at high risk for developing severe infection during the current COVID-19 epidemic. Results from clinical trials with HCQ in non-pregnant adults may not be directly extrapolated to pregnant women given the special features of the pregnancy status.

Thus, clinical research is urgently needed to improve the care and reduce the risk of poor pregnancy outcomes of women in this and in future epidemics.

## **3. Hypotheses**

- In SARS-CoV-2-infected pregnant women with non-severe COVID-19 disease, the administration of oral hydroxychloroquine for 14 days reduces viral shedding by PCR and disease progression.
- In SARS-CoV-2-infected asymptomatic pregnant women, the administration of oral hydroxychloroquine for 14 days prevents the development of COVID-19 disease.
- In SARS-CoV-2 PCR negative pregnant women in contact with a SARS-CoV-2-infected or suspected case, the administration of oral hydroxychloroquine for 14 days prevents SARS-CoV-2 infection.

## **4. Objectives**

### **Primary**

1. To assess the effect of HCQ in reducing SARS-CoV-2 viral shedding by PCR in infected pregnant women with mild symptoms.
2. To assess the efficacy of HCQ to prevent incident SARS-CoV-2 infection in pregnant women in contact with an infected or suspected case.
3. To evaluate the effect of HCQ in preventing the development of the COVID-19 disease in asymptomatic SARS-CoV-2-infected pregnant women.

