#### Primary endpoint

Number of PCR-confirmed infected pregnant women assessed from collected nasopharyngeal and oropharyngeal swabs at day 21 after treatment start (one week after treatment is completed).

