#### Secondary endpoints

##### Maternal/Foetal

1. Incidence of COVID-19 disease during pregnancy
2. Incidence of COVID-19-related admissions
3. Incidence of all-cause admissions
4. Incidence of all-cause outpatient attendances
5. Mean duration of symptoms-signs of COVID-19

6. Frequency and severity of adverse events
7. Incidence of preeclampsia
8. Incidence of gestational diabetes
9. Incidence of SARS-CoV-2 infections during pregnancy
10. Prevalence of intrauterine growth restriction (<10th centile according to local standards) (21)
11. Maternal mortality rate

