| Adherence to study medication                                                                                                                                                     |                             | x                                          | x                                                             |                        |                                      |                             |
| Ultrasound data                                                                                                                                                                   |                             |                                            |                                                               | x                      |                                      |                             |
| Infant health status check (telematics visit)                                                                                                                                     |                             |                                            |                                                               |                        |                                      | x                           |

\* In case of presence of fever and/or two symptoms suggestive of COVID-19 disease (fever, fatigue, cough (with or without sputum production), anorexia, malaise, muscle pain, sore throat, dyspnea, nasal congestion, or headache, diarrhoea, nausea and vomiting) in the previous 14 days, women will be collected a nasopharyngeal and oropharyngeal swabs for PCR analysis at any time.

\*\*In a sub-sample of participants (n=120).

\*\*\*12-24 hours of life.

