### HCQ side effects

With short-term administration (as opposed to chronic/years long use in rheumatologic disease management), the major AEs are gastrointestinal (nausea, vomiting, dyspepsia, abdominal cramps, and diarrhoea) and transient skin rashes. The gastrointestinal symptoms may vary by the specific generic manufacturer of HCQ, and are best managed by taking the drug with food or a glass of milk. A transient rash, most commonly morbilliform or psoriasiform, can develop in 10% of participants often with a sustained loading dose, and is often managed by lowering the dose. To avoid this potential side effect, this protocol is using a short loading dose, not a sustained one. Uncommonly, idiosyncratic leukopenia/ thrombocytopenia can occur and the drug should not be given to those with underlying bone marrow disorders. Lastly, hypoglycaemia can occur, and those taking insulin or glucose-lower drugs are at risk, and blood glucose should be monitored.

Manifestations of long term administration of HCQ, including retinitis, renal and hepatic disease, and cardiomyopathy are unlikely to occur in a short treatment duration such as the proposed 2-week exposure.

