#### **Statistical models and methods of analysis**

The primary analysis of the trial will be:

- The comparison of the proportion of negative SARS-CoV-2 PCR at day 14 after initiating treatment administration among those women who were SARS-CoV-2 PCR positive at recruitment in the ITT and ATP cohorts.
- The comparison of the proportion of pregnant women who were negative SARS-CoV-2 PCR at recruitment and close contacts of confirmed cases of SARS-CoV-2 infection, with a positive PCR for the infection at day 14, in the ITT and ATP cohorts.

Proportions will be compared between the two intervention-arms within each group using the Fisher exact test and presented as relative risk ratio (RR) or reduction of the RR ( $1 - RR * 100\%$ ) if RR lower than 1. Adjustment for co-variables and possible confounders will be done using Poisson regression with a log link and robust estimate of the covariance (Huber method), using the method proposed by Zou et al. 2014 and 2013.

Continuous variables will be compared between groups using Wilcoxon rank sum test and the effect presented as Mean Difference. Adjustment for co-variables and possible cofounders will be done using ordinary least square regression. Variables will be transformed to the logarithm scale if normality is improved and results presented as Proportional Difference. If after transformation, non-normality of the residuals is detected using diagnostic regression plots, robust intervals of confidence and Wald test will be presented instead.

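### Primary objective 3 (preventing COVID-19 disease in asymptomatic infected women) has no matching primary endpoint, primary analysis or sample-size basis

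*Protocol*

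**What the plan says.** The cover table (Main objectives), section 3 (Hypotheses) and section 4 (Objectives, Primary) all treat asymptomatic infected women as a separate question with a clinical outcome: "To evaluate the effect of HCQ in preventing the development of the COVID-19 disease in asymptomatic SARS-CoV-2-infected pregnant women".

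The parts of section 5 that turn objectives into tests read differently:

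- **Primary endpoint:** "Number of PCR-confirmed infected pregnant women assessed from collected nasopharyngeal and oropharyngeal swabs at day 21 after treatment start". There is no clinical component.
- **Statistical models and methods of analysis,** first primary comparison: "The comparison of the proportion of negative SARS-CoV-2 PCR at day 14 after initiating treatment administration", taken "among those women who were SARS-CoV-2 PCR positive at recruitment in the ITT and ATP cohorts". This takes in symptomatic and asymptomatic women alike.
- **Same section,** second primary comparison: contacts who were PCR-negative at recruitment, "with a positive PCR for the infection at day 14, in the ITT and ATP cohorts".
- **Sample size:** 100 asymptomatic and 100 symptomatic infected women, each randomised 1:1, justified by control cure rates of 3%, 10% and 30%. The contacts are sized on prevalence of infection. No rate of disease development is given.
- **Secondary endpoints, Maternal/Foetal,** item 1: "Incidence of COVID-19 disease during pregnancy".

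On symptoms, diarrhoea appears in the lists under Inclusion criteria and Clinical severity and in the Table 1 footnote. The footnote, which sets when an extra swab is taken, adds two more: "sore throat, dyspnea, nasal congestion, or headache, diarrhoea, nausea and vomiting) in the previous 14 days". The section on HCQ side effects says that with short-term use "the major AEs are gastrointestinal (nausea, vomiting, dyspepsia, abdominal cramps, and diarrhoea".

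**The concern.** A primary objective should lead to an endpoint, a comparison and a sample-size argument. Objective 3 leads to none that is primary. For asymptomatic infected women the primary comparison is PCR clearance, which is a different question from whether they fall ill.

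This goes beyond detail that a statistical analysis plan could supply. The Protocol itself fixes the primary endpoint and the primary comparisons. An analysis plan that follows them omits objective 3; one that adds a disease comparison departs from the Protocol. If the choice is made after data are seen, any claim on this objective, positive or null, rests on an outcome picked late. A null result would also be hard to interpret, because no power was ever stated for it.

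The symptom overlap matters once disease onset has to be defined. These women are PCR-positive at entry, so a repeat swab cannot tell a drug side effect from disease.

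**Working it through.** **1. Objective against endpoint, analysis and sizing**

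| Primary objective | Primary endpoint | Primary analysis | Sizing basis |
|---|---|---|---|
| 1. Viral shedding, symptomatic infected | PCR, day 21 | PCR-negative, day 14 | cure rate |
| 2. New infection, contacts | PCR, day 21 | PCR-positive, day 14 | infection prevalence |
| 3. COVID-19 disease, asymptomatic infected | none on disease | none on disease | cure rate |

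The first two rows match in kind but not in day. Table 1 schedules maternal swabs at enrolment and at the visit 7 days after treatment completion (day 21), and none at day 14.

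**2. The plan's own sample-size figures**

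Inputs from Sample size: two-sided 0.05, 80% power, 100/2 = 50 per arm in each infected group. Formula (normal approximation, p̄ the mean of the two rates):

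n per arm = [1.960·√(2p̄(1−p̄)) + 0.842·√(p₁(1−p₁)+p₂(1−p₂))]² / (p₁−p₂)²

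- 3% vs 33%: p̄ = 0.18, so (1.065 + 0.421)²/0.09 = 24.5, that is 25 per arm.
- 10% vs 44%: 26 per arm.
- 30% vs 69%: 25 per arm.
- Contacts, 3% vs 0%: 257 per arm, which reproduces the stated number.

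The stated cure-rate contrasts thus need about 25 per arm. At 50 per arm their power is about 98% (Fisher exact 97% to 98%). The text errs on the conservative side here. None of these figures concerns disease development, so objective 3 has no stated power to reproduce.

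**3. What 50 per arm gives for a disease endpoint**

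The control incidence of disease is an assumption, shown over a range, with HCQ assumed to halve it. Fisher power sums Bin(x; 50, p_C)·Bin(y; 50, p_H) over all pairs (x, y) with two-sided Fisher p ≤ 0.05. The last column uses the formula in step 2.

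| Control | HCQ | Fisher power, 50 per arm | n per arm for 80% |
|---|---|---|---|
| 10% | 5% | 6% | 435 |
| 20% | 10% | 20% | 199 |
| 30% | 15% | 35% | 121 |
| 40% | 20% | 52% | 82 |
| 50% | 25% | 67% | 58 |
| 60% | 30% | 83% | 42 |

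For 30% vs 15%: p̄ = 0.225, so (1.157 + 0.489)²/0.0225 = 120.5, that is 121.

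Solving the Fisher power for 80% at 50 per arm, disease must fall from 30% to about 7%, or from 50% to about 22%. At a control incidence of 10%, even complete prevention has only 38% power.

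**The case against.** **Disease is not left unanalysed.** It is a secondary endpoint, symptoms are collected at entry, during dosing and at day 21, and the methods section gives Fisher and robust Poisson methods for proportions within each group. This stands. What is missing is a place in the primary analysis and a basis for its size.

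**Cases and contacts are not pooled.** The primary endpoint reads as one count over all women, and a reader might infer that persisting infection is mixed with new infection. The methods section does not support that: it separates women positive at recruitment from negative contacts and compares arms within group. The endpoint wording is only loose.

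**The plan does not score side effects as disease.** A reader might infer that HCQ's gastrointestinal effects will be counted as COVID-19. The text shown adopts no outcome definition. The Table 1 footnote is a swab trigger that needs fever and/or two symptoms. The Clinical severity text lists diarrhoea but not nausea or vomiting, and defers to Annex 3, which is not at hand. The overlap is a reason for care in writing the definition, not an error already made. Any bias in relative risk would rest on assumed side-effect rates, so none is given here.

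**A disease primary may be underpowered.** This also stands, and it is why moving objective 3 to secondary is a legitimate answer.

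**Conclusion.** The mismatch is established from the Protocol's text alone and depends on no assumption: objective 3 is primary, and no primary endpoint, primary comparison or sizing rate addresses it. The primary analysis as written cannot answer that question.

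The power figures are illustrative, since the Protocol gives no disease incidence for this group. On the assumptions shown, 50 per arm falls short of 80% power for a halving at every control incidence up to 50%, and reaches it only at about 60%. The size of any side-effect bias cannot be derived from the documents.

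**What to change.** In Primary endpoint and in Statistical models and methods of analysis, state one primary endpoint and one intention-to-treat comparison per stratum:

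- **Symptomatic infected:** PCR clearance.
- **Contacts:** new PCR-confirmed infection.
- **Asymptomatic infected:** proportion developing COVID-19 disease within a fixed window after first dose, with PCR clearance secondary in this group.

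Reconcile day 14 in the methods section with day 21 in Primary endpoint and in Household and follow-up visits. In Sample size, add the detectable effect for the disease endpoint with its assumed control incidence. Alternatively, move objective 3 to secondary in the cover table and section 4.

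For analysis only, define disease onset so that gastrointestinal complaints alone during dosing do not meet it. All other listed symptoms, such as headache, muscle pain, chills or malaise, still count. Report an all-symptom version as a sensitivity analysis.

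The cost is mainly wording, settled before unblinding. Two downsides should be stated: a few true gastrointestinal-only cases are missed in the main definition, and, because daily calls end with the 14-day course, a window running to day 21 relies on the day-21 visit for symptoms on days 15 to 21.
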